**NIV INITIATION**

**Determine if the patient is a candidate for NPPV**

1 Conscious, maintaining airway, and breathing spontaneously for several minutes in case of mask displacement.

Also, meet at least 1 of the following criteria: >

- Respiratory distress- moderate to severe dyspnea and respiratory rate > 25 with accessory muscle use and/or paradoxical breathing and unable to speak a complete sentence with PaO2/FiO2 < 200 or SpO2< 92% on high flow mask with >15lpm oxygen flows

Select and install patient interface and breathing circuit

**Manage patient anxiety**

- Explain the goal of noninvasive ventilation
- Prearrange patient communication
- Start with low-pressure settings and hold the mask to the patient's face before tightening the strap.
- Let the patient remove the mask for a short time to speak or drink.

**Set the controls**

Adjust the settings as needed to optimize synchronization, optimize breath volume and/or PCO2, minimize fatigue of accessory muscles, relieve dyspnea, and reduce respiratory rate—the frequency goal to be ≤ 25 b/min. Titrate ventilation and oxygenation. Adjust settings as patient's condition and leak change, and adjust the alarms appropriately.

**Optimize patient comfort**

> Make sure the mask fits properly. Check repeatedly that the mask is comfortably positioned. Maintain an acceptable leak tolerance. A small leak is well compensated and should be present to prevent pressure necrosis avoid leaks >30%

**Minimize adverse effects**

Pressure sores > Check whether the mask is the right size and is appropriately positioned. Use wound care dressing, adequate upper airway humidification, heated humidifier, saline nasal spray, an oilless salve to the affected areas as needed. Excessive leakage > Adjust the interface, adjust the straps, and/or change to another type of mask.

**EPIDURAL**

Baseline PT/ INR and platelet levels should be within an acceptable range to allow epidural insertion. Insertion catheter between 9 to 2 pm on the given day per the protocolized LMWH given at 7 pm on the units: or at least 4 hrs before the next dose of UFH and 12 hours after the last dose.

**Remove** the **catheter** a minimum of 4 -6 hours after a dose of UFH. Administer the next dose of UFH no sooner than 2 hours after **catheter removal**. Once-daily low-molecular-weight heparin (LMWH).

Daily site inspection (antimicrobial incise drapes transparent dressing) is done each time the drug/ sham injection is made. The injection port is kept well covered and sealed and brought to the side near the flank/ shoulder. The epidural catheters (True or Sham) will be in situ for a minimum of 2 doses or 48 hours, whichever is more, and a maximum of 4days (96 hours of catheter and 120 hours of observation).

All asepsis will be maintained for the control group as in the Intervention group, a Local injection anesthetic will be given at the L2-L3/ L3-L4 site, and the catheter will be taped tightly to the skin and dressing done to match the intervention group.

**WEANING NIV SETTINGS**

The clinical and physiological parameters used in this setting include – arterial pH ≥ 7.35, oxygen hemoglobin saturation (SpO_2_) > 88% on FiO_2_ ≤ 60%, respiratory rate ≤ 25 / min, heart rate ≤ 120 / min, systolic blood pressure ≥ 90 mmHg, and no signs of respiratory distress like agitation, diaphoresis or anxiety.

Patients satisfying these criteria may be weaned by any method as per clinician discretion- step reduction of the duration of NIV use, stepwise reduction in pressure support, and immediate intermittent withdrawal of NIV.

**CRITERIA FOR ENDOTRACHEAL INTUBATION**

The pre-determined criteria for endotracheal intubation and mechanical ventilation (MV) to avoid delayed intubation:

1. Signs of persisting or worsening respiratory failure:

- RR > 40 cycles/min,
- Signs of respiratory-muscle fatigue (no improvement in subjective scores for > 12 hours)
- Copious tracheal secretions,
- SpO2 below 85 % for more than 5 min without technical dysfunction at Fio2 100% and best-tolerated PEEP
- Intolerance to NIV

or one of the following

1. Hemodynamic instability is defined by an SBP below 90 mmHg, MBP below 65 mmHg, or requirement for increasing vasopressor doses to maintain the same for 2 hours.
2. Deterioration of neurologic status with a Glasgow coma scale below 12 points.

For all patients, a trial of HFNO or Nonrebreather oxygen will be allowed according to the physician's preference in patients with signs of persisting or worsening respiratory failure (to rule out patient discomfort with NIV) and no other organ dysfunction before performing endotracheal intubation and invasive ventilation.

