**The interventions**

A baseline assessment of all outcome measures as appropriate will be made. Normal body temperature, RASS of -1 or 0, and VAS < 4 will be ensured by administering Midazolam ( titrated to effect) or Paracetamol as warranted.

All patients will be turned lateral or sitting position, and an injection of LA be given at L2-3 or L3-4 space. An epidural catheter will be inserted under all asepsis and fixed to the skin in the intervention group. It will be fixed firmly with antimicrobial incise drapes covering at least the lower one-third of the back. For patients who appear fidgety, catheter tunneling may also be used.

The control group will have a sham catheter fixed precisely like the intervention group but not entering the epidural space. The fixation and dressing will be similar to the intervention group.

The intervention group will be administered Injection Morphine Sulphate once every 18-24 hours into the epidural space. The doses will be escalated daily (5-10mg), titrated to the effect: escalation limited by hypoventilation resulting in respiratory acidosis (pH <7.2).

The intervention will continue for a minimum of 2 doses and a maximum of 4 doses (96 hours) of morphine. It will be stopped at 120 hours, or if: the epidural catheter gets dislodged before the second dose, the patient is weaned off noninvasive ventilation to high flow mask for a continuous period of 12 hours or requires endotracheal intubation.

The patient will be followed up till death or 28 days after ICU discharge.

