**Outcome assessment**

*Outcome measures*

TFdi, p0.1, MV, RR, Vt (average of 3 readings, ^eighth^ hourly )

Arterial blood gas and associated values-Pa o2, PaCO2, pH, HCO3, p/F ratio (at least once a day)

Spo2, Fio2, ROX index, Subjective comfort and dyspnea scores – 8^th^ Hourly

VAS, RASS, Weaning (hours off NIV on high flow mask or face mask)- (mean values over 24 hours)

Intubation- Yes/ No: Days after randomization

Length of stay in ICU

Outcome at 28 days of admission

Incidence of excessive respiratory depression (PaCO2> 45 and pH < 7.2)

Incidence of difficult/ failed epidural insertion, catheter pullouts, and complications such as bleeding/ infection/ hematoma will be documented.

Timing of outcome assessment- - Every 8^th^-hour assessment / daily / one time as detailed above

Blinding- The assessor, patient, nurses, physicians, and treating team will be blind to group allocation. One member of the team not involved in research will administer the drug.

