**NIV weanability**

Once a day, daily data will be collected as- weaned fully from NIV/ weaning from NIV ongoing/ same as yesterday/ not wean-able/ respiratory support increased/intubated)

Hours off NIV will be recorded as – 0/ <12/ 12-18/ >18 and off NIV

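### The hours-off-NIV weaning measure does not separate planned weaning from a pre-intubation trial of HFNO or nonrebreather oxygen, so rescue hours count as weaning hours

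*Protocol*

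**What the plan says.** Five places in the Protocol bear on this.

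- *Outcome assessment* lists as an outcome measure "Weaning (hours off NIV on high flow mask or face mask".
- *NIV weanability* has two records. One is a daily status with the levels "weaned fully from NIV/ weaning from NIV ongoing/ same as yesterday/ not wean-able/ respiratory support increased/intubated". The other begins "Hours off NIV will be recorded as" and gives four bands: 0, <12, 12-18, and >18 and off NIV.
- *Criteria for endotracheal intubation* states that "a trial of HFNO or Nonrebreather oxygen will be allowed", at the physician's preference, for patients whose respiratory failure persists or worsens. The purpose and limits follow: "to rule out patient discomfort with NIV) and no other organ dysfunction before performing endotracheal intubation and invasive ventilation". No maximum duration is given.
- *Weaning NIV settings* sets physiological criteria for who may be weaned, among them RR ≤ 25, SpO2 > 88% on FiO2 ≤ 60%, pH ≥ 7.35 and no signs of distress.
- *The interventions* stops study treatment when, among other events, "the patient is weaned off noninvasive ventilation to high flow mask for a continuous period of 12 hours or requires endotracheal intubation".

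Duration of NIV is also collected, under *Intubation and mortality rates*.

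**The concern.** A patient can be off NIV for two opposite reasons: recovery, or an oxygen trial as the last step before intubation. The hours field treats these as one state. A patient who is failing, or who cannot tolerate the mask, then accrues hours that read as progress, and the same hours may come off the recorded NIV duration.

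The error need not balance between the arms. The listed signs that lead to the trial include intolerance of NIV and no improvement in subjective scores for more than 12 hours. The trial is designed to see whether morphine changes respiratory drive and comfort. If it improves them, controls would have more trial hours, more apparent weaning time and possibly shorter NIV duration, which would mask a benefit. If the morphine arm had more such trials, the bias would run the other way. Blinding does not remove it, because it would arise through the treatment effect itself.

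**Working it through.** The plan gives no figure on this point, so the check compares the texts.

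1. **Does trial time meet the weaning measure?** A nonrebreather is a face mask, so time on it fits the measure in *Outcome assessment* directly. HFNO is not literally a mask, but the bands in *NIV weanability* count hours off NIV whatever the device. On a plain reading both kinds of trial are counted. Neither place makes the count depend on the reason for removing NIV.

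2. **Do the weaning criteria screen trial time out?** They would for some patients, if they were applied. RR > 40 is incompatible with RR ≤ 25, and SpO2 below 85% at FiO2 100% is incompatible with SpO2 > 88% at FiO2 ≤ 60%. Intolerance of NIV, copious secretions and unimproved subjective scores have no numerical conflict with the criteria. In either case the hours field does not refer to the criteria, so they do not restrict what is counted.

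3. **Does the daily status screen it out?** It can. It has levels for a patient who cannot be weaned, for increased support and for intubation. But no rule assigns a trial day to a level, and none ties the level to the hours band. Take a patient moved to nonrebreather oxygen for worsening failure who stays on it for 12 to 18 hours. The hours field gives the third of four bands, while the status field may say that the patient cannot be weaned. Both entries follow the text.

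4. **Does trial time reach the stopping event?** The stop needs 12 continuous hours on a high flow mask after being weaned off NIV. The trial has no time limit, so 12 hours is not ruled out. Whether such a patient has been weaned off is not stated. Nor is high flow mask distinguished from HFNO or a nonrebreather: *NIV initiation* uses the term only for a mask with flows above 15 lpm.

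5. **What is untouched?** The primary outcome is the diaphragm thickening fraction, and the 21 patients per group are derived from it alone. Intubation is recorded separately, with its day and, on conversion, its cause.

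6. **Can the size be calculated?** No. It would need the number and length of oxygen trials in each arm, and the document gives neither.

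**The case against.** The strongest reply is that the record does not ignore failure. The daily status lets staff mark a deteriorating patient as not weaned, and separate criteria govern who may be weaned. This stands in part: it rules out saying that a failing patient is simply scored as weaned, or that the Protocol has one definition of weaning that the trial satisfies. It does not repair the hours field, which uses neither safeguard.

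Second, a long and well-tolerated trial may not be failure at all. Its stated purpose is to rule out discomfort with NIV, and a patient who stays off NIV may have had only that. This stands, and it argues against scoring every trial hour as not weaned.

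Third, the outcome is minor. Weaning hours appear neither in the objectives nor among the secondary outcomes named for comparison under *Statistical analysis*. This stands and limits the weight of the point, although hours off NIV is a listed outcome measure and NIV duration is collected.

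Fourth, the coding may be settled in case report form instructions or an analysis plan not shown here. That may be so. But an analysis plan can score rescue time only if the reason for removing NIV was recorded, and the Protocol's data items do not include it.

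A reader might also infer that the Protocol stops study treatment in deteriorating patients on the ground that they are weaned. The text does not say this. It says weaned off, not merely off; the trial is framed as a step before intubation, with nothing to suggest that 12 hours or more is expected; and intubation is a stopping event in its own right. What remains is an ambiguity.

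**Conclusion.** The point holds for the hours-off-NIV measure and, through the same hours, possibly for NIV duration. As written, time on a pre-intubation oxygen trial is credited as weaning time, and the daily status can contradict it without any rule to settle which prevails. A difference between arms is plausible but not shown, and its direction is not fixed.

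No size can be given. With 25 recruited per arm, a reader might infer that each misclassified patient shifts a weaning proportion by 1/25 = 4 percentage points. The Protocol defines no such proportion and no 12-hour success threshold, so that figure describes an outcome the trial does not have.

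The conclusion rests on two readings: that the bands count all hours off NIV whatever the device, and that no instruction outside the Protocol already separates the reasons. It does not alter the definition of the primary outcome or of intubation.

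**What to change.** - Add one code to the case report form for the reason for each period off NIV: planned weaning, or an oxygen trial under the intubation criteria.
- Do not credit trial hours as weaning, in either the hours-off-NIV or the NIV-duration outcome, when the trial ends in return to NIV, intubation or death. Report the remaining trial hours separately, so that a patient whose only problem was the mask is counted neither as a failure nor as an ordinary wean.
- Reconcile *The interventions*, *Weaning NIV settings* and *Criteria for endotracheal intubation*, so that it is clear whether an oxygen trial can constitute the 12-hour weaned-off event. Which way that is settled is a clinical decision, and none is proposed here.

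The cost is one added data field, a short wording change and fewer credited weaning hours. Requiring the physiological weaning criteria to be met at the moment NIV is removed would cost more: blood gases, heart rate and blood pressure are guaranteed only about once a day, so new assessments would be needed. The reason code avoids that.

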**DATA COLLECTION**

The following data will be recorded on admission:

**Demographic & ICU admission data;**

Age, gender, Carlson's comorbidity Score, APACHE-II, Sepsis-related Organ Failure Assessment (SOFA) score, (scores range from 0 to 24, with higher scores indicating more severe organ failure), COVID markers on admission, baseline assessment, and final assessment ( Serum ferritin, IL6, CRP where available)

The number of lung quadrants involved in chest X-rays at admission or CT severity score if available.

**Physiological parameters** including respiratory rate, systolic blood pressure, and heart rate, and arterial-blood gases will be recorded at inclusion, between 12 and 24 hours after randomization and minimum once every 24 hours after that.

**Respiratory Drive and related parameters**

Once at baseline and once every 8 hours after that, the following will be assessed till the epidural catheter is in situ, or five days whichever is greater.

The researcher will do the baseline assessment, be aware of the group allocation, and insert the epidural catheter (true or sham). She/ He will mark the site of best visualization for USG probe, ensure best fit NIV interface and assess baseline subjective comfort scores.

After that, all assessments will be done by a fixed set of postgraduate ICU trainees, all trained in TFDi assessment but blinded to group allocation.

Ultrasound-guided TFDi- This procedure will be performed as described earlier.(17,19)

The patient will be supine with head-end elevated to 30 %. The right hand will be abducted and kept near the head. The diaphragm will be located by placing the transducer in the intercostal space above the right 8^th^- 11^th^ intercostal space, in the anterior- axillary line, directing the ultrasound beam perpendicular to the diaphragm. The inferior border of the costophrenic sinus will be identified at end-inspiration as the zone of transition from the lung sliding shadow to the visualization of the diaphragm and liver. The zone of apposition will be noted.

The diaphragm thickness will be recorded in time motion (TM) mode.

The sweep speed will be adjusted to obtain a minimum of three to 8 cycles on the same image.

Several diaphragm images (outlined by the two clear, bright parallel lines of the pleural and peritoneal membranes) will be located: the image will be discarded if the two bright lines are not visible. The least and maximum thickness as on eyeballing will be located and a picture stored for subsequent quantitative analysis and crosschecking by a blinded assessor.

The position of the first (baseline) USG assessment will be marked on the skin to allow all subsequent recordings from the same position.

A note will be made of the ongoing sedation dosages and ventilator settings during the measurement of TFdi (settings will be kept the minimum required for patient comfort – but will not be changed/ dictated for purposes of the study)

Airway occlusion pressures (p0.1), Respiratory rate/ min, Tidal volume (Vt) & Minute Ventilation (MV) as displayed on the ventilator at the ongoing minimal support for best patient comfort and oxygenation: observed over 1 minute, an average of 3 highest readings (ensuring a mask leak < 30%) All patients will be on Hamilton C1 ventilators.

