**Sample size**

Sample size justification A pilot study showed the mean TFDi in COVID 19 patients on PEEP 5 to be 45%(SD 15); To decrease mean fractional thickening of the diaphragm index by 30% after the dose of morphine with allocation in a 1:1 ratio, 21 patients will be needed in each group. Accounting for dropouts/ loss of data, 25 patients will be recruited in each limb.

*Statistical analysis*

Interim analyses are planned at 50% of sample recruitment, without unblinding to ensure that subjects are not being exposed to an unacceptable level of risk, whether the trial can be stopped early, check some of the assumptions that went into the original design and sample-size calculations of the trial (like within-group variability, recruitment rates, base event rates). The alpha spending strategy used will be one-fifth of the available 5 percent alpha at the interim analysis. i.e., the interim analysis p-value must be < 0.01 to stop the trial early and claim efficacy. Spend the remaining four-fifths of the 5 percent alpha at the end, or the end analysis p-value must be < 0.04 to claim efficacy. The two groups shall be compared for the mean TFdi (overall and 24^th^ hrly) by unpaired t-tests. Within-group comparison of TFdi shall be made (overall and 24^th^ hrly) by Repeated measures analyses.

Secondary outcomes- Intubation, Mortality, duration of mechanical ventilation, ICU stay, Subjective scores, Demographics, and severity of illness shall be compared by chi-square, t-tests, or nonparametric tests as suitable.

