**Sample size**

Sample size justification A pilot study showed the mean TFDi in COVID 19 patients on PEEP 5 and clinically optimal pressure support to be 45% (SD 15); To decrease this by 30% at 36 hours after the dose of morphine with allocation in a 1:1 ratio, 21 patients will be needed in each group.

Compliance and missing data- All analyses will be based on the groups as randomly allocated: an intention-to-treat analysis. A per-protocol analysis will also be done. The statistical significance will be taken as the 5% level for the top comparisons and the subsidiary comparisons, the 1% level. Patients with a P/F ratio > 150 at inclusion will be compared to those with lower values.

Data Storage- Because of the unique challenges of repeated data capture in COVID ICU, all repetitive data will be captured photographically and sent to a central data repository online to be categorized and stored by patient name and time of data capture (once every 8 hours), making in 14-time points of data capture for each patient. Data storage will be by blinded personnel.

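### No single primary TFdi comparison or averaging window is named, and the natural reading of the overall mean runs past the end of dosing and does not match the 36-hour basis of the sample size

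*Protocol*

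**What the plan says.** **Measurement.** Under *Respiratory Drive and related parameters*, the schedule for TFdi and the other drive measures reads: "Once at baseline and once every 8 hours after that, the following will be assessed till the epidural catheter is in situ, or five days". The longer of the two periods applies, so five days is the minimum.

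**Dosing.** Under *The interventions*: "The intervention group will be administered Injection Morphine Sulphate once every 18-24 hours into the epidural space", and "The intervention will continue for a minimum of 2 doses and a maximum of 4 doses (96 hours) of morphine". The same section then stops the intervention at 120 hours, or earlier for dislodgement before the second dose, weaning or intubation. The *EPIDURAL* section keeps the true or sham catheter in for at least two doses or 48 hours, whichever is more, and for "a maximum of 4days (96 hours of catheter and 120 hours of observation".

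**Analysis.** Under *Statistical analysis*: "The two groups shall be compared for the mean TFdi (overall and 24^th^ hrly) by unpaired t-tests". No window is given for the overall mean, and neither comparison is named as the primary one.

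**Sample size.** The *Sample size* text in the detailed methodology takes mean TFdi 45% (SD 15) and a 30% fall at 36 hours after the dose, needing 21 per group. The first *Sample size* section gives the same numbers without a time and recruits 25 per group. *Data Storage* describes 8-hourly capture "making in 14-time points of data capture for each patient".

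**The concern.** The collection window, the dosing window, the tested quantity and the sample-size quantity are four different things. An average over all scheduled readings would mix readings under morphine with readings after it has worn off, in proportions set by how many doses each patient received and how far apart. A real effect of the planned size would then look smaller than the one the trial was sized for. The result would also be hard to interpret, since it is neither an effect at a stated time nor an effect over a stated treatment period. With two candidate comparisons and no primary named, the choice could also be made after the data are seen.

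**Working it through.** **1. The plan's own figure.** The planned difference is 0.30 × 45 = 13.5 points, with SD 15. A two-sample t calculation (noncentral t, two-sided 5%, power 80% assumed because the protocol states none) gives exactly 21 per arm; power at 21 is 0.81. The figure reproduces, for a single reading per patient.

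**2. Where 36 hours falls.** 36/8 = 4.5 and 36/24 = 1.5. Counted from baseline, 36 hours is neither an 8-hourly nor a 24-hourly reading. The protocol does not say which dose starts the clock.

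**3. Time points.** Including baseline, 8-hourly capture gives 96/8 + 1 = 13 points to 96 h and 120/8 + 1 = 16 to 120 h. The stated 14 fits neither.

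**4. Off-drug share.** There are 15 post-baseline readings at 8, 16, ..., 120 h. Cover ends at (doses − 1) × interval + duration of effect. Duration is not in the protocol, so two values are shown: 24 h, and 36 h (a literal reading of the sample-size wording).

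| Course | Off drug, 24 h effect | Off drug, 36 h effect |
|---|---|---|
| 4 doses, 24-hourly | 3/15 (20%) | 2/15 (13%) |
| 4 doses, 18-hourly | 6/15 (40%) | 4/15 (27%) |
| 3 doses, 24-hourly | 6/15 (40%) | 5/15 (33%) |
| 3 doses, 18-hourly | 8/15 (53%) | 6/15 (40%) |
| 2 doses, 24-hourly | 9/15 (60%) | 8/15 (53%) |
| 2 doses, 18-hourly | 10/15 (67%) | 9/15 (60%) |

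With 18 h of effect the range is 27-73%. With 48 h, two doses still leave 40-47% off drug, but four doses 24-hourly leave none.

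**5. Power of a 120-hour mean.** Assume the full 13.5 points while on drug, zero afterwards, and every treated patient on the same course. Diluted difference = 13.5 × (1 − off-drug share). SD of a mean of m readings = 15 × √((1 + (m − 1)ρ)/m), with ρ = 0.6 assumed. For m = 15 this is 15 × √(9.4/15) = 11.9. With 21 per arm, two-sided 5%:

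| Off drug | Difference | Power, SD 11.9 | Power, SD held at 15 |
|---|---|---|---|
| 20% | 10.8 | 0.82 | 0.62 |
| 40% | 8.1 | 0.58 | 0.40 |
| 60% | 5.4 | 0.30 | 0.21 |
| 67% | 4.5 | 0.22 | 0.16 |

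The SD 11.9 column is the relevant one, because averaging removes within-patient variance. With 25 per arm and the stated final significance level of 0.04, that column becomes 0.86, 0.62, 0.31 and 0.23.

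**6. A 0-48 h mean.** Six readings; SD = 15 × √((1 + 5 × 0.6)/6) = 12.2. For an undiluted 13.5 points, power is 0.94 (0.84-0.96 for correlations from 0.9 down to 0.5). Under 24 h of effect, one of the six readings (hour 48) is off drug after two doses 18 h apart. If every patient followed that course, the difference would be 13.5 × 5/6 = 11.25 and power 0.83.

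**7. The 24-hourly comparisons.** At hour 24, a patient dosed 18-hourly is 6 h past dose 2, and one dosed 24-hourly is 24 h past dose 1. At hour 96 after four doses, the gaps are 96 − 54 = 42 h and 96 − 72 = 24 h.

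**The case against.** - **The 120-hour average is inferred.** The protocol never says that the overall mean runs to 120 h, and an analysis plan that is not shown may set the window. This stands as a limit on the claim. But the protocol itself states the comparison, the collection schedule and the 36-hour sizing, and these do not fit together as written.
- **The dilution rests on an assumed duration.** Also true. A reader might infer that the primary effect is diluted by 20-67%. The documents do not support that: the range needs 24 h of effect with abrupt loss, and its upper end describes a patient who receives only two doses 18 h apart, not a trial average. No distribution of doses is given.
- **The power loss may be small.** A reader might take power to fall to 0.62 or even 0.16. Those values ignore the variance that averaging removes, and 0.16 also needs every treated patient to stop at two doses. On the full 24-hourly course, power is about 0.82, close to the plan's 0.81.
- **No untreated tail is proven for every patient.** Catheter removal is not loss of effect, and with 48 h of action a full 24-hourly course leaves no reading off drug.
- **A fixed-horizon mean that keeps readings after stopping is a legitimate intention-to-treat quantity.** Agreed, provided that it is chosen openly and the trial is sized for it; here the sizing is at 36 hours.
- **The 24-hourly and repeated-measures analyses would show early effect and late loss.** In part. They do not say which comparison decides the trial. Their mixed times since dose follow from flexible dosing and are not in themselves an error.

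**Conclusion.** The point holds as a mismatch to be repaired. No primary TFdi comparison or window is fixed, the natural reading of the overall mean extends beyond dosing, and the sample size rests on a different time. The off-drug share is 20-67% or 13-60% across dosing patterns for 24 or 36 h of effect, both assumed. The cost in power runs from little against the planned 80% (0.82, all on the full 24-hourly course) to severe (0.22, all on two doses 18-hourly), with 0.58 at 40% off drug, against 0.94 for an undiluted 48-hour mean. These figures rest on 21 per arm, two-sided 5%, correlation 0.6, 24 h of effect and abrupt loss. That the mismatch exists is certain from the text; how much it would dilute the result is not.

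**What to change.** 1. Under *Statistical analysis*, name one primary TFdi comparison over a fixed window counted from the first true or sham injection, the same in both arms and containing 36 hours; for example, the mean of the six scheduled readings to 48 h. Restate the sample-size basis for that quantity.
2. Analyse it as randomised, whatever doses were received. A window tied to each patient's own dosing would depend on weaning or intubation after randomisation. The exclusion list, which includes patients given fewer than two doses, should be squared with this.
3. Report the full five-day mean, the readings after 48 h and those after the last injection as secondary. Record the clock time of each true or sham injection and label each reading by hours since injection.
4. Reconcile *The interventions*, *EPIDURAL*, *Respiratory Drive and related parameters* and *Data Storage* on 96 versus 120 hours, and on 14 versus 13 or 16 time points.

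**Cost.** Wording, plus a recorded injection time; no extra patients or TFdi readings. The primary mean uses fewer readings per patient. It also leaves out the later, escalated doses, so if the effect grows with escalation the 48-hour mean may be smaller than the five-day mean. That should be stated in the plan. If the sponsor prefers the five-day mean as primary, the sample size should be derived for it.

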**Detailed methodology, with definitions**

**PATIENTS**

- Inclusion: 18 -80 years of age; met all 4 of the following criteria
  - **RR** > 25 breaths per minute; **PaO2/FiO2** < 200mmHg while the patient was breathing oxygen at a flow rate of ≥ 10 liters per minute for at least 15 minutes;
  - **On NIV PSV6 PEEP 5** with < 30% leak**, Minute ventilation > IBW x10mlx25/min** (e.g., for 50 kg individual = 12.5 lpm)
  - **Rule out pain, fever, discomfort**

If any present:

Manage with (when in doubt, all can be given together-)

Injection PCM 1gm- stat for pain/discomfort and /or fever,

Injection Midazolam 1 mg iv stat for anxiety,

Midazolam to be followed by Infusion Dexmedetomidine 400 mcg in 50 ml at 3-5 ml per hour, titrated to blood pressure ( MAP >65 mmHg or and effect.

*And* active patient counseling to comfort and reassure)

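### p0.1, minute ventilation, RR and tidal volume are given two reading rules, and the highest-3 rule records a near-maximum that shifts with variability and, for per-breath readings, with respiratory rate

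*Protocol*

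**What the plan says.** Under Outcome assessment, Outcome measures, the protocol lists "TFdi, p0.1, MV, RR, Vt (average of 3 readings", taken every eight hours. It does not say how the three are chosen.

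Under Detailed methodology, Respiratory Drive and related parameters, p0.1, RR, Vt and MV are read "as displayed on the ventilator at the ongoing minimal support" and are "observed over 1 minute, an average of 3 highest readings", with mask leak kept below 30%. TFdi is not covered by this rule. The same section gives it a separate ultrasound method.

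Neither place refers to the other. The protocol does not say whether a reading is one breath, one refresh of the display or a running average.

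**The concern.** Three readings taken without regard to size estimate the typical level over the minute. The three largest estimate something close to the maximum. That second quantity depends on three things: the true mean, the spread of readings within the minute, and the number of readings there were to choose from. A treatment that changes the spread or the number of readings changes the recorded value even when the mean is unchanged. Applying the same rule in both arms does not remove this, because the arms may come to differ in exactly those two features.

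The treatment is meant to lower respiratory drive, and RR is itself one of the outcomes compared. If each reading is a breath, a slower patient offers fewer candidates for the top three, so Vt and p0.1 tend to be recorded lower. The error favours morphine.

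There is also a practical problem. Several trainees take the readings at 14 time points per patient. If some follow one section and some the other, one column of the dataset holds two different quantities. Photographs of the display would not show whether the values kept were the highest of the minute.

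**Working it through.** **The plan's own figure.** The only figure that can be reproduced is the sample size, for TFdi: "To decrease mean fractional thickening of the diaphragm index by 30" per cent from a mean of 45 (SD 15), a difference of 0.30 × 45 = 13.5 points. Sidedness and power are not stated; I assume two-sided 5% and 80%.

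n = 2(1.960 + 0.842)² × 15² / 13.5² = 19.4, so 20 per group. The t-test version gives 20.4, so 21, which is the stated number. The sample size does not depend on the reading rule.

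**Inputs for the reading rule.**
- Respiratory rates: entry at RR "> 25 breaths per minute"; on NIV, "the frequency goal to be ≤ 25 b/min"; intubation criterion "RR > 40 cycles/min". The values 20, 30 and 35/min are my illustrations around these.
- Within-minute CV of Vt or p0.1: not given. Assumed 10–40%.
- Readings: normal and independent, one per breath, so that k readings in the minute equals RR.

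**Step 1: upward shift.** Let e(k) be the expected mean of the three largest of k standard normal readings (400,000 simulated minutes per k). Three unselected readings have an expected shift of 0 at any k.

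| k | 20 | 25 | 30 | 35 | 40 |
|---|---|---|---|---|---|
| e(k), SDs | 1.468 | 1.585 | 1.675 | 1.748 | 1.811 |

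Overstatement of the level = CV × e(k). From k = 20 to 40 this is 15–18% at CV 10%, 29–36% at 20%, 44–54% at 30% and 59–72% at 40%.

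**Step 2: part that depends on rate.** With the true mean and CV unchanged, the apparent fall when the rate goes from a to b is 1 − [1 + CV·e(b)] / [1 + CV·e(a)].

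Example, 35 to 25 at CV 20%: 1 − (1 + 0.2 × 1.585)/(1 + 0.2 × 1.748) = 1 − 1.317/1.350 = 2.4%.

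| Assumed CV | 35 → 25/min | 40 → 20/min |
|---|---|---|
| 10% | 1.4% | 2.9% |
| 20% | 2.4% | 5.0% |
| 30% | 3.2% | 6.7% |
| 40% | 3.8% | 8.0% |

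**Step 3: correlated breaths.** With first-order autocorrelation 0.5, e(20) = 1.386 and e(40) = 1.750, a gap of 0.36 SD. At 0.8 they are 1.167 and 1.565, a gap of 0.40 SD. The independent case gives 1.811 − 1.468 = 0.34 SD. Correlation lowers the overall shift but does not shrink the gap.

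**Step 4: part that depends on variability.** At 30 readings the overstatement is 33.5% at CV 20% and 50.2% at CV 30%. If the CV went from 30% to 20% with mean and rate unchanged, the recorded value would fall by 1 − 1.335/1.502 = 11%. This route does not need the rate to change.

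**The case against.** *It may be a refinement, not a contradiction.* The outcome list is a summary. The other text stands under a heading that promises definitions, and an average of the three highest is still an average of three. That reading is possible, so a reader who infers a flat contradiction goes further than the text. But nothing says that one section governs, and if the detailed rule does, the problem with selecting by size remains.

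*The link to respiratory rate is not established for all four variables.* It needs the number of readings to equal the number of breaths. That is natural for Vt and plausible for p0.1. RR and MV are per-minute quantities and may be shown as running or timed values, and the protocol says only that they are as displayed. This objection stands. For RR and MV one can say only that the rule pushes values upward by an amount set by their variability.

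*The size rests on assumptions.* It does: no CV is stated, and the rate changes are illustrations. The large overstatement of levels is not in itself a difference between arms.

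*The artefact of slowing appears only if RR truly falls*, and RR is reported separately, so the trial would already be showing a fall in drive. This also stands for the rate-dependent part. The artefact would exaggerate a supporting result, not create the trial's conclusion. It would still let p0.1 or Vt partly repeat the RR finding while looking like separate evidence.

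**Conclusion.** The point holds as a correction to secondary drive measures. Two rules are stated for the same four variables, and they estimate different quantities. The highest-3 rule overstates the typical level by about 1.5–1.8 within-minute SDs for 20–40 independent readings, and by more in absolute terms the more variable the readings are. If a reading is one breath, slowing alone would lower recorded Vt or p0.1 by about 1–4% (35 to 25/min) or 3–8% (40 to 20/min), at an assumed CV of 10–40%.

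A reader might infer that the whole rule is biased by respiratory rate, or that any fall in p0.1 and Vt on morphine would be an artefact. The protocol supports neither: the display's behaviour is not described, and the rate-dependent part is modest under every CV tried. Nor does the point reach the primary endpoint. TFdi has its own ultrasound method, and the 21 per group is unaffected.

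**What to change.** In Respiratory Drive and related parameters:
- delete the word highest;
- define a reading for each variable (one breath, one display refresh or a running average);
- state one rule that does not select by size: the mean over the full minute, or three readings at preset times, with leak below 30% and the reading repeated if leak exceeds that.

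In Outcome measures, refer p0.1, MV, RR and Vt to that rule. Keep TFdi out of it and point it to the ultrasound method, since a timed rule for a ventilator display would conflict with measurement from several cycles on one image.

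The cost is one or two sentences. Recorded absolute levels will be lower than under the highest-3 rule, and no clinical management changes.
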